### Inclusion and exclusion criteria (Aim 1)

The inclusion criterion is continuous fee-for-service Medicare enrollment for at least 12 months prior to AF diagnosis or matched index date (July 1 of inclusion year) for controls and continuous enrollment in fee-for-service (FFS) Medicare after AF diagnosis/index date for at least 12 months or until death if death occurred before 12 months of continuous enrollment.

Patients with prevalent AF will be identified as follows:ICD-9-CM code 427.31 or ICD-10-CM code I48 in 2 outpatient claims or 1 inpatient claim within 365 days, in any diagnosis position of the claim [16–18]. The index date will be the date of the first qualifying inpatient claim or second qualifying outpatient claim. Patients will be required to have 12 months of FFS claims without an AF diagnosis prior to the index AF claims based on inclusion criteria.

Exclusion criteria are:

patients with any claim for CRAO in the 12 months prior to AF diagnosis or index date for controls (July 1 of potential inclusion year).

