### Inclusion and exclusion criteria (Aim 2)

Inclusion criteria are fee-for-service Medicare enrollment for at least 12 consecutive month and 12 months FFS with Part A, B, and D enrollment following the index date for at least 12 months or until death, and presence of atrial fibrillation as defined in the exposure section. The index date for patients exposed to anticoagulation will be the date of the first anticoagulant prescription drug claim occurring after the diagnosis of AF. For potential controls, only patients with no exposure to anticoagulation throughout the study period would be eligible to avoid selecting controls who start an anticoagulant during the follow-up period. For controls, inclusion and exclusion criteria will be examined for each year after AF diagnosis, and the midpoint of one random year will be selected as the index date for each control patient.

Exclusion criteria include:

Patients with any claim for CRAO in the 12 months prior to AF diagnosis or index date for controls;Patients who die within first 12 months of enrollment;Patients taking therapeutic-dose heparin, enoxaparin, dalteparin, fondaparinux, or betrixaban.

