^†††^ The Quan, 2005 algorithm uses ICD-9-CM 362.34 (transient retinal artery occlusion) and ICD-10-CM H34.0 (transient retinal artery occlusion) as part of the algorithm for identifying cerebrovascular disease; we have removed these specific codes from our comorbidity list due to the possibility that CRAO may have been miscoded as 362.34 or H34.0 due to similar clinical presentation.

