1) We will repeat the primary analysis, classifying CRAO based on the presence of the ICD codes in any diagnosis position rather than the primary diagnosis position.2) We will perform a sensitivity analysis for any retinal artery occlusion, using ICD-9-CM codes 362.3, 362.30, 362.31, 362.32, 362.33 and ICD-10-CM codes H34.9, H34.233, H34.1x, H34.0x, H34.12, H34.13, H34.23x, H34.21x) [31].i) We will perform a secondary analysis of patients with CRAO who later developed atrial fibrillation, to assess the hypothesis that clinically undetected paroxysmal AF may be associated with CRAO.j) Table shell for Aim 1 regression results are provided in Tables 6 and 7. The primary outcome is underlined.k) To address confounding resulting from patients potentially receiving a competing therapy (left atrial appendage occlusion, a procedural alternative to long-term oral anticoagulation), we will exclude patients with ICD-9-CM procedure code 37.90 or ICD-10-CM 02L73DK either in the follow-up period or in the ascertainment period.

**Table 6 pone.0296251.t006:** Crude and adjusted rates of CRAO in patients with and without atrial fibrillation.

	AF		No AF		AF	No AF	Rate Difference (95% CI)	aHR (95% CI)
	Patients with event	Rate per 1000 Or 100,000 Person-years	Patients with event	Rate per 1000 Or 100,000 Person-years	Adjusted rate per 1,000 person-years	Adjusted rate per 1,000 person-years		
CRAO (Overlap weighted)								
CRAO (primary Dx)								
Any RAO								
Ischemic stroke								
UTI								

**Table 7 pone.0296251.t007:** Hazard ratios for atrial fibrillation vs. no atrial fibrillation for Aim 1.

Outcome	Unadjusted Model	Adjusted Model†
CRAO (Overlap weighted)	HR (95% CI)	aHR (95% CI)
CRAO (primary dx)	HR (95% CI)	aHR (95% CI)
Any RAO	HR (95% CI)	aHR (95% CI)
CRAO (any dx position)	HR (95% CI)	aHR (95% CI)
Ischemic Stroke	HR (95% CI)	aHR (95% CI)
UTI	HR (95% CI)	aHR (95% CI)

^†^This column reflects the results of a model that incorporates overlap weighting using propensity scores re-estimated after our first stage matching procedure.

We will report a figure showing the adjusted cumulative incidence of CRAO according to AF vs. No AF groups using an overlap-weighted cumulative incidence function.

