#### Regression modeling (aim 2)

a) In keeping with target trial emulation methodology as described above, the index date for patients exposed to anticoagulation will be the date of the first anticoagulant prescription drug claim occurring after the diagnosis of AF. For potential controls, only patients with no exposure to anticoagulation throughout the study period would be eligible to avoid selecting controls who start an anticoagulant during the follow-up period. For controls, inclusion and exclusion criteria will be examined for each year after AF diagnosis, and the midpoint of one random year will be selected as the index date for each control patient.b) Similar to Aim 1, patients diagnosed with CRAO precedent to or concurrent to AF diagnosis will be excluded and these patients will be examined in an exploratory analysis.c) Our primary analysis will utilize propensity score overlap weighting methodology to approximate a randomized design where baseline hazard of CRAO of patients receiving anticoagulation vs. not receiving is comparable. We will incorporate the following variables to define the propensity score: age, time since first AF claim, sex, geography, race, Medicaid dual eligibility, vascular comorbidities and non-vascular comorbidities relevant to the likelihood that a patient will be treated with anticoagulation (to include all of the comorbidity variables included for Aim 1 propensity score, as well as history of gastrointestinal bleeding or peptic ulcer disease (using validated ICD-9-CM codes 531.x (gastric ulcer), 532.x (duodenal ulcer), and 578.x (gastrointestinal hemorrhage) and their ICD-10-CM counterparts K25.x, K26.x, and K92.2) and history of intracranial hemorrhage (any of ICD-10-CM I60, I61, S06.3, S06.4, S06.5, S06.6 and their ICD-9-CM counterparts 430.x, 431.x, 432.x)) [32–35].d) Our principal effect of interest is the hazard of CRAO among patients treated with any oral anticoagulant agent compared to those not treated. Given variable patient adherence to anticoagulation, we will take advantage of the strength of Part D data (which records pharmaceutical fills rather than prescriptions) and treat anticoagulation exposure as a time-varying covariate for patients exposed to anticoagulation.e) We will perform identical sensitivity analyses as described in Aim 1.f) Table shells for the results of Aim 2 are shown in Table 8.

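### The any-retinal-artery-occlusion sensitivity analysis counts codes that the baseline exclusion never clears, so old occlusions can be scored as new events

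*Protocol article*

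**What the plan says.** **Outcome.** Regression modeling (aim 1), item h(2), states "We will perform a sensitivity analysis for any retinal artery occlusion". The codes it gives are "any retinal artery occlusion, using ICD-9-CM codes 362.3, 362.30, 362.31, 362.32, 362.33" together with "ICD-10-CM codes H34.9, H34.233, H34.1x, H34.0x, H34.12, H34.13, H34.23x, H34.21x". Regression modeling (aim 2), item e, carries the same sensitivity analyses into Aim 2. Tables 6, 7 and 8 each have an Any RAO row.

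**Baseline exclusion.** Under Inclusion and exclusion criteria (Aim 1) the only eye-related exclusion is "patients with any claim for CRAO in the 12 months prior to AF diagnosis or index date for controls". The Aim 2 criteria say the same: "Patients with any claim for CRAO in the 12 months prior to AF diagnosis or index date for controls". Regression modeling (aim 2), item b, restates it in terms of CRAO alone: "patients diagnosed with CRAO precedent to or concurrent to AF diagnosis will be excluded".

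**Setting.** The Outcome section describes the primary event as incident and accepts outpatient as well as emergency and inpatient claims, with the code in the primary position. Item h(2) does not restate setting or position.

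**Adjustment.** No retinal occlusion code appears in Table 2, and its footnote on cerebrovascular disease explains that the transient codes 362.34 and H34.0 were taken out.

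**The concern.** A time-to-first-event analysis needs a cohort free of the event at time zero, at least within the look-back. The protocol accepts this for CRAO and for AF, each of which gets a 12-month clean period. It then widens the outcome in h(2) without widening the clean period. A retinal occlusion can generate further claims when the eye is reviewed, and outpatient claims can count. An occlusion coded before index can therefore reappear afterwards and be taken for a new one.

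At stake is the Any RAO row in both aims. Its purpose is to show whether the CRAO result holds under a broader outcome definition. If some of its events are old, agreement or disagreement with the CRAO result is harder to read. Matching and overlap weighting do not repair this, because earlier retinal occlusion is not among the covariates.

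**Working it through.** **Step 1: set the code lists side by side.** The exclusion says CRAO without codes; I read it as the Outcome section's codes, 362.31 and H34.1x.

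| Codes | Cleared before index? | Counted in any-RAO? |
|---|---|---|
| 362.31 / H34.1x (CRAO) | yes | yes |
| 362.3, 362.30, 362.32, 362.33 | no | yes |
| H34.9, H34.21x, H34.23x | no | yes |
| H34.0x (transient) | no | yes |
| 362.34 (transient) | no | not listed |

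The middle three rows are the mismatch. They comprise unspecified, branch and partial occlusion codes in both coding eras, and transient codes under ICD-10 only. ICD-9 runs from January 2000 to September 2015, that is 15.75 of 21 study years (75%). In that period a transient code is not an any-RAO event unless 362.3 is read as a stem.

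**Step 2: direction of the bias.** Let E be the new events in the unexposed group, P the carried-over events there, R the true ratio, and k the ratio of carried-over events between the groups. Then

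observed ratio = (R·E + k·P) / (E + P),

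a weighted average of R and k. With k = 1 it moves toward 1. With k = R it is unchanged but partly made of old events. With k above R it is inflated.

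**Step 3: illustration of size.** The protocol gives no any-RAO rate and no prevalence of earlier occlusion, so there is no plan figure to reproduce. From Sample size calculation I take 285,000 per group, CRAO rates of 22 and 11 per 100,000 per year, and a ratio of 2. The following are assumptions:

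- any-RAO rates are double the CRAO rates (44 and 22 per 100,000);
- 0.05% to 0.2% of each group have an earlier non-CRAO occlusion code (k = 1);
- 10% to 50% of those are coded again after index;
- no loss to follow-up.

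New events in one year: 285,000 × 44/100,000 = 125.4 and 285,000 × 22/100,000 = 62.7. Carried-over events per group: 285,000 × 0.0005 × 0.10 = 14.25, up to 285,000 × 0.002 × 0.50 = 285.

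| Follow-up | Low carry-over | High carry-over |
|---|---|---|
| 1 year | (125.4 + 14.25)/(62.7 + 14.25) = 1.81; 13% of events old | (125.4 + 285)/(62.7 + 285) = 1.18; 75% old |
| 5 years | (627 + 14.25)/(313.5 + 14.25) = 1.96; 3% old | (627 + 285)/(313.5 + 285) = 1.52; 38% old |

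If earlier occlusion is instead twice as common in the AF group, the one-year high case gives (125.4 + 570)/(62.7 + 285) = 2.00, with 855 of 1,043.1 events (82%) old.

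**Step 4: a more cautious prevalence.** The assumed any-RAO rate leaves 22 − 11 = 11 per 100,000 per year for non-CRAO occlusion in the unexposed. If the look-back year holds only that share (0.011%) in each group, 285,000 × 0.00011 = 31.35 patients, giving 3.1 to 15.7 carried-over events per group. The one-year ratio is then 128.5/65.8 = 1.95 to 141.1/78.4 = 1.80. The five-year ratio is 630.1/316.6 = 1.99 to 642.7/329.2 = 1.95.

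**The case against.** The best defence is that this is one sensitivity analysis in a condensed article, that the study outcome is called incident, and that cohort handling for such an analysis is often left to a fuller plan. Its place as a sensitivity analysis limits the importance of the point. The appeal to condensation does not stand: the exclusion and the outcome codes are both given, they disagree, and nothing in the text widens the look-back or requires the first listed code to fall after index.

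Other parts of the defence stand:

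- **Not every such patient is counted.** A later claim must carry a listed code. If h(2) inherits the primary-position rule, some follow-up visits would not qualify. The text supports only that such patients can be counted.
- **Transient occlusion is not affected throughout.** 362.34 is absent from the ICD-9 outcome list.
- **The size is not known.** A look-back prevalence of 0.05% to 0.2% is about 4.5 to 18 times the 11 per 100,000 used in Step 4. Repeat visits can push prevalence above incidence, but the documents do not support any particular multiple.
- **The row is not worthless.** In every illustration above the observed ratio stays above 1.

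A reader might also infer a leak in the primary CRAO endpoint. The Table 2 footnote drops the transient codes "due to the possibility that CRAO may have been miscoded as 362.34 or H34.0", so a patient with such a code before index might seem to have had CRAO already. The footnote speaks of a possibility. Leaving a doubtful code out of the adjustment set does not make it established prior CRAO. A patient with a transient code and a later CRAO claim may be having a first CRAO, and excluding that patient could discard a true event.

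**Conclusion.** The mismatch is real and follows from the protocol's own code lists. It affects the any-RAO sensitivity analysis in Aim 1 and, by reference, in Aim 2. The documents do not show that it affects the primary CRAO analysis.

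The bias is toward no effect when earlier occlusion is equally common in both groups. When it is more common in one group, old disease feeds the ratio, and the result can be attenuated, unchanged or inflated. The range of 1.18 to 1.99 for a true ratio of 2 rests on an assumed any-RAO rate, prevalence, recoding share and follow-up, with equal history in the two groups. It shows that the effect could be trivial or substantial and is not an estimate for this study. The correction is worth making because it is cheap and the row is meant to support the main result.

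**What to change.** In item h(2), and for Aim 2 through item e, add a clean period matched to the outcome. For the any-RAO analysis only, in both groups, exclude patients with any code on that outcome's list in the 12 months up to and including index. Clear 362.34 as well. It is the ICD-9 counterpart of the listed H34.0x, and a patient coded 362.34 before the switch could later be counted under H34.0x. State whether the primary-position rule applies to the any-RAO outcome. Re-estimate the propensity scores in the reduced sample so that the overlap weights still balance the covariates.

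The cost is one more code list, one more weighting run, and a few patients: on the assumed 0.05% to 0.2%, 285 to 1,140 of 570,000. Occlusions last coded more than 12 months before index are still missed, so carry-over is reduced but not abolished.

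The primary CRAO exclusion need not change. At most, excluding patients with an earlier 362.34 or H34.0x code could be offered as an optional sensitivity analysis of the CRAO result.

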### Biological rationale

The prevailing paradigm is that CRAO arises because of ipsilateral stenotic carotid plaque [3] releasing predominantly calcium or cholesterol emboli. However, this observation is drawn from studies evaluating patients with branch retinal arterial occlusion (BRAO) where emboli may be visualized on funduscopic examination [4]. This may have falsely increased the perceived contribution of calcium/cholesterol emboli to CRAO as these emboli are less likely to autolyze when compared with fibrin-based emboli and are thus visible longer. Recently, we demonstrated that tissue plasminogen activator (tPA, a drug that breaks up fibrin-based clots) improved the rate of visual recovery in some patients with CRAO, providing evidence against the assertion that CRAO is caused exclusively by cholesterol or calcium emboli [5–7]. Furthermore, over 50% of people with CRAO do not have high-grade ipsilateral carotid stenosis [8] and 30% of people with CRAO do not have even mild ipsilateral carotid disease [9].

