### Outcome

The outcome of interest is incident central retinal artery occlusion. Central retinal artery occlusion will be identified through ICD-9-CM 362.31, which we validated in a prior study [13] in the primary diagnosis position in any emergency department, inpatient, or outpatient claim. We will use the corresponding ICD-10-CM code H34.1x for claims occurring after September 31, 2015.

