#### Regression modeling (aim 1)

a) The study index date will be the date of the first AF claim in the study and July 1 in the first year of inclusion in the analytic cohort for controls for the purposes of our survival analysis.b) We will describe cumulative incidence of CRAO over time with the overlap-weighted cumulative incidence function and presented graphically for patients with and without atrial fibrillation. Next, a weighted, unadjusted cause-specific hazard model will be fit with AF as the univariable predictor and CRAO as the event of interest, with patients censored at death, at end of data availability, or at end of fee-for-service Medicare enrollment.c) Then, a weighted cause-specific hazard model, clustered by state, and adjusting for age, sex, race, cardiovascular comorbidities will be fitted. Directly adjusted cumulative incidence curves for AF and control patients will be created with adjustment for all model covariates [28].d) We will test the proportional hazards assumption for all models.e) Our primary analytical model will be an overlap-weighted model with propensity scores derived from the adjustment covariates previously described as predictors for the presence of atrial fibrillation. We will report our results with sequential adjustment to produce the fully-adjusted, weighted model. We employ this sequential adjustment strategy to provide insight as to sources of measured confounding.f) We will evaluate **positive control endpoints**. Our positive control endpoints will be any ischemic stroke (defined by ICD-9-CM 434.0, 434.00, 434.10, 434.11, 434.9, 434.90, 434.91, 436/ ICD-10-CM I66.09, I66.19, I66.29, I66.9, I63.40, I63.50, I67.89 in the primary diagnosis position in a hospitalization or ED visit) [29]. We will utilize the same modeling strategy as used for the primary outcome.g) We will evaluate **negative control (falsification) endpoints**. Our negative control endpoint will be hospitalized/ED urinary tract infection (including renal abscess and pyelonephritis) (ICD-9-CM 590.1, 590.11 590.2, 590.8 or 599.0/ ICD-10-CM N15.1, N39.0, N10). We will utilize the same modeling strategy as used for the primary outcome [30].h) We will perform several sensitivity analyses for outcome ascertainment.

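### The any-retinal-artery-occlusion analysis is listed as an ascertainment check but changes the condition counted, and it covers the protocol's one named miscoding only on the ICD-10 side

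*Protocol article*

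**What the plan says.** **Primary outcome.** The Outcome section fixes CRAO by one code per era: "Central retinal artery occlusion will be identified through ICD-9-CM 362.31, which we validated in a prior study", with H34.1x taking over after September 2015.

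**Stated purpose of item h.** In Regression modeling (aim 1), item h opens: "We will perform several sensitivity analyses for outcome ascertainment". Two follow.
- h(1) keeps the CRAO codes and relaxes only the claim position: "classifying CRAO based on the presence of the ICD codes in any diagnosis position rather than the primary diagnosis position".
- h(2) changes the code list. Its ICD-9 part reads: "We will perform a sensitivity analysis for any retinal artery occlusion, using ICD-9-CM codes 362.3, 362.30, 362.31, 362.32, 362.33". For the later years the list given is: "ICD-10-CM codes H34.9, H34.233, H34.1x, H34.0x, H34.12, H34.13, H34.23x, H34.21x".

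Aim 2, item e, carries the same analyses over. Tables 6 to 8 each have one row for any retinal artery occlusion (RAO), beside the CRAO rows.

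**Named miscoding.** The third footnote to Table 2 explains why two transient-occlusion codes were dropped from the cerebrovascular comorbidity definition: "due to the possibility that CRAO may have been miscoded as 362.34 or H34.0 due to similar clinical presentation".

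**Branch occlusion.** Biological rationale says of the carotid-plaque account of CRAO that "this observation is drawn from studies evaluating patients with branch retinal arterial occlusion (BRAO) where emboli may be visualized on funduscopic examination", and adds: "This may have falsely increased the perceived contribution of calcium/cholesterol emboli to CRAO".

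**The concern.** A sensitivity analysis for ascertainment holds the condition fixed and varies how it is detected. h(1) does that. h(2) adds other conditions, among them branch and partial occlusion. If its HR differs from the CRAO HR, there are at least two explanations: some added claims are CRAO recorded under another code, or atrial fibrillation (AF) acts differently on the other occlusions. One pooled row cannot tell them apart, although the heading of item h suggests the first.

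The code list also does not match the miscoding that the authors themselves foresee. If CRAO may be recorded as transient occlusion, an ascertainment check should include the transient codes in both coding eras. As written, h(2) includes them in one.

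At stake is whether the robustness analysis can be interpreted, in both aims. The primary CRAO result is not at stake.

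**Working it through.** The document gives no figure for the any-RAO analysis, so there is none to reproduce. The check has two parts.

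**1. Code lists side by side**

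| Group | ICD-9-CM in h(2) | ICD-10-CM in h(2) |
|---|---|---|
| Central (primary outcome) | 362.31 | H34.1x (H34.12 and H34.13 also listed) |
| Transient (paired in the Table 2 footnote) | 362.34 **not listed** | H34.0x listed |
| Branch | 362.32 | H34.23x (H34.233 also listed) |
| Partial | 362.33 | H34.21x |
| Parent or unspecified | 362.3, 362.30 | H34.9 |

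The footnote supplies the transient labels and the Outcome section the central ones. The branch, partial and unspecified labels are ordinary ICD usage; the article does not spell them out.

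The study period is 2000–2020 (Design and setting), and ICD-10 codes apply after September 2015. Taking whole calendar years, the ICD-9 era is 15 years 9 months of 21 years: 189/252 months = 75% of calendar time. The share of person-time may differ. In that era h(2), as listed, adds branch and partial occlusion but not the named miscoding.

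**2. What one pooled HR can show**

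Inputs:
- CRAO HR 2 and control rate 11/100,000 per year, both from Sample size calculation.
- Control rate of the added codes: not given; assumed to be k × 11/100,000, with k from 0.25 to 2.
- HR of the added codes: not given; assumed 0.8 to 2.5.

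For rare events the pooled HR is the average of the two HRs weighted by control rate:

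HR_pooled = (HR_CRAO + k × HR_added) / (1 + k)

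With k = 1:
- HR_added 0.8: (2 + 0.8)/2 = 1.40
- HR_added 1.0: (2 + 1.0)/2 = 1.50
- HR_added 1.5: (2 + 1.5)/2 = 1.75
- HR_added 2.0: (2 + 2.0)/2 = 2.00
- HR_added 2.5: (2 + 2.5)/2 = 2.25

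With HR_added = 1.0 and k varied:
- k = 0.25: 2.25/1.25 = 1.80
- k = 0.5: 2.5/1.5 = 1.67
- k = 1: 3/2 = 1.50
- k = 2: 4/3 = 1.33

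The same pooled value has more than one explanation. A pooled HR of 1.75 at k = 1 requires HR_added = 1.5. That arises in either of these ways:
- No added event is miscoded CRAO, and the other occlusions have an HR of 1.5.
- Half of the added control-arm events are miscoded CRAO (HR 2) and half are other occlusions with HR 1.0: 0.5 × 2 + 0.5 × 1.0 = 1.5.

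So a move from 2.00 to 1.75 does not separate miscoding from a different AF effect.

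**The case against.** **The protocol's view of branch occlusion is hedged.** A reader might infer that the protocol rejects carrying branch-occlusion evidence over to CRAO. It does not say so. Biological rationale says only that such evidence may have inflated the perceived role of calcium and cholesterol emboli, and the reason given is that those emboli stay visible longer. It makes no claim that AF acts differently on branch and central occlusion. This stands.

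**No reading of a shifted HR is promised.** A reader might also infer that a lower any-RAO HR would be reported as an ascertainment failure. No section sets such a rule; only the heading of item h points that way. This stands too.

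**Widening to the parent category is ordinary practice.** The footnote explains a change to a comorbidity list. It does not list every way CRAO can be miscoded, and confusion between central and branch codes is not ruled out. This is a fair reason to keep the composite. It does not make the composite interpretable alone.

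**The parts can be recovered.** CRAO has its own rows, and Table 6 gives counts and rates by AF status for CRAO and any RAO, so a rough subtraction is possible for aim 1. The remainder would still mix branch, partial, unspecified and (in ICD-10) transient codes. Table 8 has HRs only, so nothing can be subtracted for aim 2.

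**The bare 362.3 might be meant as a stem.** It would then take in 362.34. But the same item marks its stems with an x, and 362.3 has none. The ambiguity is itself worth removing.

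**Conclusion.** The point holds as a minor one. h(2) is listed under outcome ascertainment but counts a broader condition, so a change in its HR is not attributable to miscoding or to a different AF effect without further rows. Its ICD-9 list omits 362.34 while its ICD-10 list includes H34.0x, so the composite is not the same outcome in the two eras, and the named miscoding is covered in only one of them.

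The size of any shift cannot be found from the document. The range of 1.40 to 2.25 rests on a CRAO HR of 2, equal control rates for CRAO and the added codes, and an assumed added-code HR of 0.8 to 2.5. The pooled HR could fall, rise or, at an added-code HR of 2, not move. It would be wrong to conclude that attenuation is expected: that follows only if the added codes have a smaller HR than CRAO. The primary outcome, the primary model and h(1) are untouched.

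**What to change.** In item h, its aim 2 counterpart (item e) and Tables 6 to 8:
1. Add an ascertainment analysis of CRAO plus transient and unspecified codes, matched across ICD-9-CM and ICD-10-CM. This means adding 362.34 to pair with H34.0x; it is not in the present outcome list.
2. Report branch occlusion (362.32 / H34.23x) in its own row.
3. Keep any RAO, but describe it as a broader secondary composite, align its two code lists, and state whether 362.3 is an exact code or a stem.

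The cost is one or two more secondary estimates per table, one newly extracted code and some regrouping. No change to the cohort, the weighting or the primary analysis is needed.
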